## Methods

### Study Design

Project Debunk has gathered data in the following 2 phases: (1) qualitative research for text message development and (2) a randomized trial. This research protocol briefly describes the methods used for the message-development phase and outlines the detailed information about the trial phase at baseline and 1 week after message exposure (ie, the intervention).

In design, the trial is being conducted as a 6-month-long randomized trial comparing 8 arms, based on the combination of the 3 message structures: framing, depth, and appeal (Figure 1). Participants are randomly assigned to one of the 8 arms. They are receiving text messages in 2 separate waves or campaigns. Each campaign consists of 2 text messages per day for 30 days (ie, 60 text messages). The 2 campaigns are 2 months and 1 week apart.

Allowing for a crossover design, participants within each of the 8 arms are randomly divided into 2 groups: group 1 is receiving text messages about conventional tobacco products during campaign 1 and then about NETP during campaign 2. Group 2 is receiving text messages about NETP during campaign 1 and then about conventional tobacco during campaign 2. This crossover design was advised by the Tobacco Center of Regulatory Science on Youth and Young Adults (TX TCORS) Scientific Steering Committee, as it will allow us to explore potential differences between the 2 categories of products within and between participants, with respect to their perceived risk of tobacco use. Data collection for the trial is being conducted at baseline, 2 months post campaign 1 (PC1), 2 months post campaign 2 (PC2), weekly throughout each campaign (a weekly manipulation check assessment), and 7 days after each campaign.

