### Sample Size Determination

For sample size determination, we conducted a power calculation using the outcome of change in perceived risk of cigarette smoking from baseline to 2 months after each of the campaigns. The 8 study arms define a 2×2×2 analysis of variance (ANOVA) factorial design. Assuming a balanced design in each of the 8 study arms for the change in perceived risk, with n=70 per arm, we have at least 80% power to detect an effect size of 0.12 in a fixed-effects ANOVA. A total of 560 participants are needed to provide 70 participants per study arm at 2 months PC2, with complete measurements at baseline. We assume 11% attrition between the assessment at 7 days after the program and 2 months after the program and 1.5% attrition between baseline and the assessment at 2 months PC2 (ie, a total of 12.5% attrition). As a result, our retention rate is expected to be 87.5%. This assumes 640 participants randomized to 8 study arms. This sample size was calculated using PASS 2005 (NCSS, LP).

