### Planned Data Analysis

Once the trial is complete, we plan to conduct an exploratory analysis to identify which combination of message characteristics (ie, depth, framing, and appeal) most increases perceived risk of using each type of tobacco product. This analysis is exploratory because to date no theoretical framework or empirical evidence has been presented that demonstrates the importance of one message structure over another in the context of tobacco risk communication. We will first conduct, a series of 8 repeated-measures mixed-effects models for each type of tobacco product with the interaction effect (group [one combination vs all other combinations] × time [baseline, 2 months PC1, and 2 months PC2]) to predict perceived risk of using the product. These models will control for past 30-day use of the product at baseline and the crossover group assignment. In addition to the main outcomes analyses, we plan to conduct several moderation analyses, including the examination of different groups such as gender, race, mental health status, and personality types. This analysis will allow us to check if different types of individuals may respond differently to certain structures of text messages. Repeated-measures mixed-effect models with interaction effects will be conducted. For all data analysis, *P*<.05 is considered statistically significant. We will use STATA version 14 software (StataCorp LLC) for all analyses.

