### Anticipated Results

On the basis of previous pilot data collected by our team [62], we anticipate adequate feasibility and satisfaction among participants. In a previous study that we conducted with young adult college students [61], the recruitment rate was high (80.1%) and participants reported positive changes in their perceived risk of tobacco use. We anticipate similar results in Project Debunk for all groups. We project that all message structure combinations will result in an increase in perceived risk of using tobacco products. As suggested by recent reports [4,87], we expect higher levels of perceived risk of using combustible cigarettes compared with NETP such as e-cigarettes and hookah. In addition, change over time in perceived risk is expected to be lower for combustible cigarettes, compared with e-cigarettes and hookah. We cannot predict or anticipate specific results with respect to which message structure is most effective in improving tobacco risk perception. This study will be the first to provide empirical evidence that highlights the importance of one message structure over another in the context of tobacco risk communication. Once the successful types of text messages have been identified, our future plan is to introduce the messages in the context of an advanced digital intervention that can effectively communicate tobacco risk.

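### With crossover group entered only as a covariate, each product's PC1 arm effect averages participants already messaged and not yet messaged on that product

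*Protocol article*

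**What the plan says.** The Study Design section states that "participants within each of the 8 arms are randomly divided into 2 groups". One sequence is described thus: "group 1 is receiving text messages about conventional tobacco products during campaign 1 and then about NETP during campaign 2". The other is its mirror image: "Group 2 is receiving text messages about NETP during campaign 1 and then about conventional tobacco during campaign 2". The Figure 1 legend puts a one-week break between the PC1 survey and the start of campaign 2. The reason given for the crossover is that "it will allow us to explore potential differences between the 2 categories of products within and between participants".

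The Planned Data Analysis section specifies eight mixed models per product. The tested interaction is "group [one combination vs all other combinations] × time [baseline, 2 months PC1, and 2 months PC2", and no other interaction is named for the main outcome. Crossover group has one role: "These models will control for past 30-day use of the product at baseline and the crossover group assignment".

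The Sample Size Determination section bases power on "change in perceived risk of cigarette smoking from baseline to 2 months after each of the campaigns". It claims at least 80% power for an effect size of 0.12 with 70 participants per arm at 2 months PC2 (560 in all, from 640 randomised).

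**The concern.** Take cigarettes. At PC1, group 1 has had a campaign about conventional products and group 2 has had one about NETP only. For hookah or e-cigarettes the roles are reversed. So for every product, only one crossover group in each arm has received the relevant messages when PC1 is measured.

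A crossover main effect raises or lowers a sequence by the same amount at baseline, PC1 and PC2. The difference that matters appears at PC1 and not at baseline, and it may differ by arm. A covariate of that form cannot carry it.

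The aim is to find which combination most increases perceived risk of each product. If the PC1 coefficient is pulled towards the response of people not yet messaged on that product, a real difference between message structures can be missed. The Conclusions say the results would be evidence for choosing messages in larger campaigns, so a missed difference has consequences even in an exploratory analysis.

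**Working it through.** **Inputs.** From Sample Size Determination: N = 560 evaluable (8 × 70), f = 0.12, power at least 80%, attrition 12.5%. From Planned Data Analysis: two-sided 5% level. From Study Design and the Figure 1 legend: the sequences and timing. Not given in the article, so assumed: a 1:1 split within arm; spillover *s*, the fraction of the arm effect on a product's perceived risk seen in people messaged only on the other category; and persistence *p*, the fraction of the effect left at about 5 months.

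**Plan's own figure.** Power comes from the noncentral F with λ = N·f² = 560 × 0.0144 = 8.06. With 1 and 552 df this gives 80.9%, which reproduces the claim. The 7-df omnibus test would give 49.9%, so the stated power is for a 1-df factorial effect. Also 560 / 0.875 = 640, as stated.

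**Timing.** From the end of campaign 1 to PC2 is 2 months + 1 week + 30 days + 2 months, a little over 5 months. From the end of campaign 2 to PC2 is 2 months.

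**PC1.** With half of each arm messaged on the product, f at PC1 = 0.12 × (0.5 + 0.5*s*):

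| *s* | f | λ = 560·f² | Power, 1 df |
|---|---|---|---|
| 0 | 0.060 | 2.02 | 29% |
| 0.25 | 0.075 | 3.15 | 43% |
| 0.50 | 0.090 | 4.54 | 57% |
| 0.75 | 0.105 | 6.17 | 70% |
| 1 | 0.120 | 8.06 | 81% |

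The planned contrasts set one arm against seven, 70 against 490. There the effect detectable with 80% power is 2.80 × √(1/70 + 1/490) = 0.36 SD. If that effect is halved, power is 28.8%, so the proportional loss is the same.

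**PC2.** Everyone has now been messaged on both categories, and only time since exposure differs. With f = 0.12 × (0.5 + 0.5*p*), power is 81% for *p* = 1 and about 57% for *p* = 0.5 (f = 0.09, as in the third row).

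**Does the covariate help?** One simulated data set of 16,000 participants used a 1:1 split, no spillover, full persistence and a true arm effect of 0.20 once messaged on the product.

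- Arm × time plus a crossover main effect: 0.092 (SE 0.014) at PC1, 0.202 at PC2.
- The same model without the crossover covariate: identical coefficients.
- With arm × time × crossover: at PC1, 0.213 (SE 0.019) in the messaged sequence and 0.213 − 0.243 = −0.03 in the other.
- Aligned contrast from that last model: the messaged sequence at PC1 gives 0.2133, and the other sequence at PC2 gives 0.2062 − 0.0094 = 0.1968. Their mean is 0.205, against a true 0.20.

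**Why combine sequences.** Using only the messaged half at PC1 (n = 280, f = 0.12) gives 51.6% power. Combining both sequences at their own 2-month visit restores N = 560 and λ = 8.06, about 81%, if the effect is the same in both.

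**The case against.** The strongest reply is that the size of the loss is unknown. By PC1 every participant has had 60 tobacco-harm messages in the assigned structure, so zero spillover is the extreme case, and full spillover would remove the PC1 loss. The sample size is also set for PC2, when everyone has been messaged on both categories. Both points stand. The 29% figure is a lower bound for PC1 under a 1:1 split, not the power of the trial.

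It can also be said that the analysis is exploratory and that an article condenses its plan. That carries less weight here, because the article states the model, names its interaction and gives crossover group its role. Followed as written, the model dilutes the PC1 effect unless spillover is full.

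Several stronger readings are tempting but unsupported:

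- *The plan misses its own stated estimand.* No section defines the target as 2 months after the product's own campaign. The wording in Sample Size Determination fits calendar PC1 and PC2, and both are estimated.
- *A joint 2-df test of arm × time shows a further loss from mixing.* With full persistence (and a correlation of 0.5 between the two changes), its noncentrality is 8.06, the same as for the aligned 1-df test. The drop from 0.81 to 0.72 is then only the cost of the second degree of freedom.
- *The campaign's effect is claimed without a control.* Anticipated Results says "We project that all message structure combinations will result in an increase in perceived risk of using tobacco products". That is a projection, not a planned test, and the stated objective is to compare message structures.
- *The purpose of the crossover is abandoned.* The article says only that category differences will be explored, and a condensed article need not list every such analysis.

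**Conclusion.** The point holds. As specified, each product's PC1 arm × time coefficient is an average over participants messaged and not yet messaged on that product, and its PC2 coefficient averages over about 2 and about 5 months since that product's campaign. This follows from the article's own sequence, timing and model statements and needs no outside figure.

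A reader might infer that the arm comparisons are biased by confounding. They are not, because sequence is randomised within arm. The PC1 effect is diluted towards the response of those not yet messaged on the product.

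The size rests on assumptions the article does not settle. With a 1:1 split, PC1 power for the designed effect runs from 29% with no spillover to 81% with full spillover. PC2 power depends on persistence: 81% if full, about 57% if half.

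**What to change.** In the Planned Data Analysis section:

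1. For each product, add crossover × time and arm × time × crossover terms to the mixed model.
2. Name as the main contrast the arm effect on change from baseline to 2 months after the campaign that covered the product, combined across sequences. For conventional products this is PC1 in group 1 and PC2 in group 2; for NETP it is the reverse.
3. Report the arm effects by sequence as well. The later sequence will already have received the other category's messages, 120 messages in all against 60, so the two halves of the combined contrast do not have identical histories. This is a small price.
4. As an inexpensive addition, report the group 1 against group 2 contrast at PC1 for each product. It is a randomised estimate of the product-specific message effect, conservative if there is spillover. With 280 against 280 it detects 2.80 × √(2/280) = 0.24 SD with 80% power.

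A time-varying indicator of having been messaged on the product is not an equivalent substitute for step 2. It keeps the earlier sequence counted as exposed at PC2 and so mixes 2- and 5-month effects again.

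The cost is a change of wording and a recoded time variable. Sequence is already randomised, and the surveys are already scheduled.

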**Conclusions:**

This study confirms that the recruitment, randomization, and message composition have been successfully implemented. Further analyses will identify specific types of messages that are more effective than others in increasing the perceived risk of tobacco use. If our results suggest that any of the 8 specific message structures are more effective for helping young adults understand tobacco risk, this would provide evidence to include such messages as part of a larger technology-based campaign such as mobile phone apps, entertainment-based campaigns, and social media.

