#### Follow-Up Surveys

Follow-up surveys for the trial are ongoing. Weekly manipulation check surveys will assess perceptions of participants about text messages received in the previous week. The perceived message characteristics to be assessed include loss framing [73], message complexity level [74], emotional level of messages [50], credibility [75], message enjoyment [76,77], relevance [78], and message readability.

Surveys completed by participants 7 days after each of the 2 campaigns will assess self-reported attention to the text messages [79], emotional involvement [79], thought provocation [80], motivation to discuss the messages with others [81,82], and recall of actual discussions with others about the messages and tobacco [82].

Two months PC1 and 2 months PC2, we will measure perceived risk of using each tobacco product as the main outcome [83]. As secondary outcomes, we will also measure the status and frequency of tobacco use [84], susceptibility to use tobacco products among nonusers (ie, likelihood to initiate use at some point in the future) [85], perceived addictiveness of products [4], perceived popularity of tobacco use [4], and perceived benefits of tobacco use [86].

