Enjoyment of messages (8-point scale)	5.90 (1.49)	5.87 (1.46)	5.78 (1.37)	6.13 (1.57)	5.93 (1.46)	5.93 (1.54)	5.78 (1.47)	5.96 (1.56)	5.80 (1.53)	.90
Perceived relevance (5-point scale)	2.37 (0.85)	2.37 (0.87)	2.40 (0.91)	2.38 (0.81)	2.57 (0.79)	2.22 (0.81)	2.41 (0.83)	2.26 (0.94)	2.40 (0.81)	.40
Perceived readability (5-point scale)	3.46 (0.78)	3.41 (0.81)	3.44 (0.84)	3.51 (0.75)	3.45 (0.85)	3.53 (0.70)	3.50 (0.75)	3.36 (0.84)	3.49 (0.71)	.93

^a^Missing values are not presented in this table. Out of 636 participants, 530 (530/636, 83.3%) completed the manipulation check survey.

^b^Participants were randomized to one of the 8 treatment arms, describing the type of messages.

^c^CGE: complex, gain-framed, emotional.

^d^CGR: complex, gain-framed, rational.

^e^CLE: complex, loss-framed, emotional.

^f^CLR: complex, loss-framed, rational.

^g^SGE: simple, gain-framed, emotional.

^h^SGR: simple, gain-framed, rational.

^i^SLE: simple, loss-framed, emotional.

^j^SLR: simple, loss-framed, rational.

^k^Significance testing with analysis of variance.

**Table 4 table4:** Baseline risk communication outcomes for the entire sample and by treatment arm.

Outcome^a^	Mean (SD)								
	Total	CGE^b^	CGR^c^	CLE^d^	CLR^e^	SGE^f^	SGR^g^	SLE^h^	SLR^i^
Perceived risk of using cigarettes	3.69 (0.55)	3.76 (0.49)	3.68 (0.52)	3.78 (0.35)	3.68 (0.6)	3.57 (0.65)	3.70 (0.56)	3.75 (0.47)	3.60 (0.63)
Perceived risk of using cigars	3.61 (0.56)	3.67 (0.49)	3.64 (0.5)	3.63 (0.52)	3.62 (0.56)	3.51 (0.62)	3.65 (0.56)	3.62 (0.54)	3.52 (0.67)
Perceived risk of using smokeless tobacco	3.48 (0.60)	3.49 (0.57)	3.44 (0.60)	3.59 (0.49)	3.47 (0.68)	3.45 (0.61)	3.48 (0.60)	3.56 (0.53)	3.38 (0.68)
Perceived risk of using hookah	3.09 (0.8)	3.00 (0.87)	3.15 (0.71)	3.37 (0.72)	3.09 (0.79)	2.99 (0.84)	3.13 (0.79)	3.11 (0.77)	3.01 (0.85)
Perceived risk of using e-cigarettes	3.06 (0.83)	2.98 (0.82)	3.17 (0.65)	3.31 (0.77)	3.08 (0.8)	2.98 (0.9)	3.11 (0.84)	3.04 (0.84)	2.96 (0.94)
Perceived personal benefits of e-cigarettes	0.88 (0.76)	0.87 (0.77)	0.88 (0.73)	1.02 (0.87)	0.76 (0.65)	0.91 (0.8)	0.85 (0.77)	0.89 (0.72)	0.85 (0.74)
Perceived general benefits of e-cigarettes	1.41 (0.69)	1.47 (0.51)	1.53 (0.68)	1.42 (0.69)	1.39 (0.72)	1.45 (0.78)	1.31 (0.77)	1.37 (0.73)	1.38 (0.64)
Perceived addictiveness of products	1.23 (0.59)	1.23 (0.53)	1.26 (0.56)	1.33 (0.59)	1.21 (0.64)	1.24 (0.55)	1.18 (0.62)	1.23 (0.61)	1.18 (0.61)

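### Eight one-versus-rest tests for each of five products, all judged at an unadjusted P<.05, can produce a significant message combination by chance about a third of the time within one product

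*Protocol article*

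**What the plan says.** Planned Data Analysis commits to "a series of 8 repeated-measures mixed-effects models for each type of tobacco product with the interaction effect" of "group [one combination vs all other combinations] × time [baseline, 2 months PC1, and 2 months PC2". Each model controls for baseline past-30-day use of the product and for crossover group. The section then sets one rule for everything, moderation analyses included: "For all data analysis, *P*<.05 is considered statistically significant".

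Follow-Up Surveys defines the main outcome product by product: "we will measure perceived risk of using each tobacco product as the main outcome". Table 4 reports that outcome for cigarettes, cigars, smokeless tobacco, hookah and e-cigarettes.

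Research Objectives and Planned Data Analysis both call the work exploratory, on the ground that no theory or evidence favours one structure. The Conclusions of the Abstract nevertheless say that if any of the eight structures proves more effective, "this would provide evidence to include such messages as part of a larger technology-based campaign". The Conclusions of the Discussion repeat this, and Anticipated Results plans to carry the successful message types into a digital intervention.

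**The concern.** The analysis is a screen for a winner. Eight contrasts are run for each product, each is read at 0.05, and a combination that passes is a candidate for wider use. The stated rule contains no overall test, no adjustment over the eight and no lead product.

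A threshold of 0.05 suggests to a reader that a chance finding is a one-in-twenty event. For the set of eight it is not. At stake is a message type carried forward on a false positive, with an effect estimate that is too large because it was picked for being extreme.

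**Working it through.** **Inputs from the article.** Eight combinations and the 0.05 threshold (Planned Data Analysis); five products (Table 4); 70 per arm, 560 in total, effect size 0.12, at least 80% power (Sample Size Determination). **Assumptions:** effect size 0.12 is Cohen's f; no combination truly differs; the correlation between products of the change in perceived risk, which the article does not give, is varied from 0 to 0.9.

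**1. The plan's own figure.** The noncentrality is λ = N·f² = 560 × 0.12² = 8.064, with 560 − 8 = 552 error degrees of freedom.
- 1-df factorial effect at 0.05: power 80.9%. This reproduces the stated 80%.
- 7-df overall comparison of the eight arms at 0.05: power 50.0%. This does not.

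So the sample size matches a single factorial effect.

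**2. Number of tests.** 8 × 5 = 40. Expected number with P<.05 under no difference: 40 × 0.05 = 2.0, counting both directions.

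**3. Independence bound.** 1 − 0.95⁸ = 33.7% for one product; 1 − 0.95⁴⁰ = 87.1% for all 40.

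**4. Allowing for dependence.** With equal arms, the eight one-versus-rest contrasts have mutual correlation −1/7. Simulation with 100,000 replicates, using the 2-df group × time test:

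| Family | Any P<.05 | At least one favourable P<.05 |
|---|---|---|
| One product (8 tests) | 32.6% | 18.7% |
| Five products, correlation 0 | 85.8% | 64.3% |
| Five products, correlation 0.5 | 79.2% | 58.2% |
| Five products, correlation 0.7 | 71.3% | 50.4% |
| Five products, correlation 0.9 | 56.7% | 37.5% |

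A 1-df version differs by about one point (for example 65.6% favourable at correlation 0 and 37.2% at 0.9). Hence the favourable range of about 37% to 66%.

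**5. Effect of adjustment.** With Bonferroni over the eight (0.05/8 = 0.00625), the simulated chance of any false positive within one product is 4.7%. Holm has the same first step, so under no true difference it gives the same figure.

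**6. Cost of adjustment.** For one arm against the other seven, f = d × √(1/8 × 7/8) = 0.331d.
- At 0.05: d = 0.12/0.331 = 0.36 SD for about 80% power.
- At 0.00625: 80% power needs f = 0.152, so d = 0.152/0.331 = 0.46 SD.
- At f = 0.12, power falls from 80.9% to 53.8% at 0.00625, and to 34.4% with Bonferroni over all 40 (0.05/40 = 0.00125).

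**The case against.** The strongest reply is that the study is declared exploratory, and that this is its primary objective rather than an afterthought. Unadjusted testing in exploratory work is common and debated. The language about next steps is conditional, and the larger campaign lies in the future. This softens the point. It does not remove it, because the article pairs the label with a fixed significance rule and says a positive result would be evidence for inclusion in campaigns.

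A second reply is that multiplicity procedures often sit in a full protocol or analysis plan that is not shown. That is fair, and the absence of a procedure is not the complaint. The complaint is the stated rule, which covers all data analysis.

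A third reply is that the plan asks its question separately for each product, so pooling five products into one family is the reader's choice. This stands, and it is why the single-product figure leads here.

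Some stronger readings are tempting but not supported:
- A reader might infer that the plan will pick a most effective message by chance more often than not. That needs no true difference, pooling across products, and a between-product correlation of about 0.7 or less. A significant interaction may equally mark a worse combination, and the article gives no correlation.
- A reader might count four moderators times 40 models as at least 160 further tests. The article promises only several moderation analyses, with examples, and does not say that each is crossed with every model.
- A reader might conclude that cigarettes must be the lead product because the power calculation used them. Anticipated Results expects less change for combustible cigarettes than for e-cigarettes and hookah.

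**Conclusion.** The concern holds in a limited form. If the eight combinations are truly equal, the stated rule gives at least one significant result in about 33% of trials for a single product, and one that favours some combination in about 19%. Pooling the five products raises these to about 57% to 86% and about 37% to 66%, over an assumed between-product correlation of 0.9 to 0. The figures rest on equal arms and on no true difference; where real differences exist they do not apply as stated. Moderation analyses at the same threshold add to the error by an amount that cannot be fixed from the text.

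The exploratory label would be enough if results were reported as leads for a later trial. It is not enough where a P<.05 is meant to support wider use of the selected message.

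**What to change.** For each product, fit one mixed model with all eight arms instead of eight separate ones. Begin with the three factorial effects (framing, depth, appeal) × time, which are the effects that match the stated power, or with one overall arm × time test. Call an individual combination significant only after Holm or max-t adjustment over the eight. Report findings across products, and all moderation analyses, with intervals and as hypothesis-generating, without a significance claim unless they are adjusted.

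The change is to analysis wording only, and the article says data collection is still under way. The costs are these:
- With Bonferroni over eight, the 80%-power difference for one combination rises from about 0.36 to 0.46 SD. Holm and max-t cost no more than this.
- A 7-df overall gate has only about 50% power at f = 0.12, so the factorial effects or direct Holm/max-t adjustment are the better first step.
- The factorial main effects do not by themselves say which combination is best, so the adjusted comparisons are still needed. Three independent factorial tests at 0.05 also carry 1 − 0.95³ = 14.3% error, so Holm over the three is advisable if they are to support a claim.
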